### Statistical analysis

Initially, descriptive analysis will be completed for all study variables: mean (standard deviation) for continuous variables with a normal distribution, median (interquartile ranges) in the case of non-normal distribution and the frequency (percentage) of categorical variables. Differences between the intervention and control groups will be assessed using the χ2 or Fisher exact test for categorical variables and Student *t* for continuous variables with normal distribution, or nonparametric Mann–Whitney U test, as appropriate. Differences between means, medians, or ratios at the beginning and end of the two-year follow-up period (pre- and post-intervention) will be compared using the McNemar test, Student *t* for paired tests, or Wilcoxon test, as appropriate.

The percent change with respect to baseline value is used as a measure of the pre- and post-intervention change in categorical variables, calculated as the final percentage minus the initial percentage × 100.

The intervention effect after one year of follow-up will be evaluated using the decrease in the EVITA variable and increase in the RETIRA variable. To assess the effect of the intervention model, a multilevel logistic regression analysis will be performed, considering intervention vs control group as the independent variable. The analysis will be adjusted for potential predictive independent variables and, for those considered clinically relevant, for baseline values.

To determine the economic impact of new prescriptions of cholesterol-lowering drugs in primary prevention prescribed during the study period, a descriptive analysis of costs and resource use will be completed for each study group and the groups will be compared (discount rate: 3%). The incremental cost-effectiveness ratio will be calculated as the difference between the cost average for the 2 study groups, divided by the difference between the effects for both groups. Acceptance curves will be calculated to determine the cost-effectiveness of the intervention compared to usual practice.

Significance will be established at the 5% level. All analysis will be done using Stata/SE, version 10.1 (StataCorp).

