### Study population

Twelve PCC are excluded because their current participation in a different intervention could invalidate the results of this study. The research team will identify all patients aged 35 to 74 years who received a new prescription for cholesterol-lowering drugs from the remaining 271 PCC during the study period (October 1, 2011-September 30, 2013), as recorded in the electronic medical records system, known as ECAP. Exclusion criteria are any history of cardiovascular disease (ischemic heart disease, cerebrovascular accident, or peripheral artery disease) recorded in ECAP and patients for whom pharmacy records showed receipt of a cholesterol-lowering prescription drug during the 12 months preceding their inclusion in the study.

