### Randomization

The unit of randomization is the PCC. This avoids a possible contamination effect if different health professionals from the same PCC were randomized to different study groups. Cluster randomization will be done by random-sized blocs of PCCs (i.e., 2,4,6,8,10), stratified in quartiles by a synthetic PCC quality care indicator, “EQA” [23]. This method will ensure that each study group has the same number of PCCs and GPs and that there is a balanced distribution of the EQA covariate between the two groups [24,25].

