### Sample size

The preliminary study conducted by the research team showed the availability of a sample size of approximately 60,000 new statin treatments prescribed each year. Assuming 90% strength, 5% alpha error, a 1:1 ratio of control to intervention participants, corrected by the cluster design and assuming 10% loss to follow-up, our study could detect a difference of 1% (according to the medical criteria applied by the experts on the research team) at a 90% confidence interval. Even with this strength level, a clinically relevant difference of 10% can be established.

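### The stated between-arm tests ignore the randomised centres, no cluster-aware method is given for COST, the paired tests do not fit patient-level new starts, and the percent-change formula does not match its label

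*Protocol article*

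**What the plan says.** Under Randomization, the protocol article states: "The unit of randomization is the PCC".

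The Statistical analysis section opens with a descriptive analysis of all variables. In the same paragraph it says "Differences between the intervention and control groups will be assessed using the χ2 or Fisher exact test for categorical variables", with Student t or Mann-Whitney tests for continuous variables. Pre/post differences "at the beginning and end of the two-year follow-up period (pre- and post-intervention) will be compared using the McNemar test", a paired t test or a Wilcoxon test. The unit of pairing is not given. The section closes with a 5% significance level for everything.

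The next paragraph defines a percent change relative to baseline, "calculated as the final percentage minus the initial percentage", times 100.

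The section then assigns the intervention effect, described through EVITA and RETIRA, to a multilevel logistic regression. The abstract says that the descriptive analysis is aggregated by GP and that the intervention effect is estimated by multilevel analysis. Costs have a paragraph of their own: description by group, a comparison of the groups by an unstated method, a cost-effectiveness ratio and acceptability curves.

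Study population excludes patients for whom "pharmacy records showed receipt of a cholesterol-lowering prescription drug during the 12 months preceding their inclusion in the study".

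**The concern.** Patients of one PCC share GPs, local prescribing habits and the same allocation, so their outcomes are correlated. χ2, Fisher, t and Mann-Whitney tests treat each observation as independent. With any positive ICC their standard errors are too small and p-values below 0.05 come too often. The sample size text says that it corrects for the cluster design, but these tests do not.

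Three further matters follow from the same section.

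- **Outcomes outside the model.** COST is a monetary amount and cannot be the response of a logistic model, although lower health care cost is part of the primary objective. REGISTER is not mentioned with the model in Statistical analysis.
- **Paired tests.** McNemar and the paired t test need the same unit measured twice. New starts in the two years come from largely different patients.
- **Percent change.** A quantity labelled as relative to baseline is computed without dividing by the baseline.

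**Working it through.** **1. Size of the unadjusted tests.** The plan gives no ICC or design effect, so it has no figure of its own to reproduce here.

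Inputs from the document:
- Centres: "from the remaining 271 PCC during the study period" (Study population).
- Volume: "approximately 60,000 new statin treatments prescribed each year" (Sample size).
- Loss to follow-up: 10% (Sample size).

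Cluster size: 60,000 × 0.9 / 271 = 54,000 / 271 ≈ 199.3 per PCC per year. Without the loss it is 60,000 / 271 ≈ 221.4.

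Formulas, for equal cluster sizes and a two-sided test: design effect DE = 1 + (m − 1) × ICC; true error of a nominal 5% test = 2 × (1 − Φ(1.96 / √DE)). The ICCs are assumptions.

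| Assumed ICC | DE (m = 199.3) | True error | True error (m = 221.4) |
|---|---|---|---|
| 0.001 | 1.20 | 7.3% | 7.6% |
| 0.005 | 1.99 | 16.5% | 17.6% |
| 0.01 | 2.98 | 25.6% | 27.4% |
| 0.02 | 4.97 | 37.9% | 39.9% |
| 0.05 | 10.91 | 55.3% | 57.2% |

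Example, ICC 0.01: DE = 1 + 198.3 × 0.01 = 2.98; 1.96 / √2.98 = 1.135; 2 × (1 − Φ(1.135)) ≈ 0.256.

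If the tests are run on GP summaries, the observations per cluster are GPs. Both the number of GPs per PCC (k, 8 to 15) and the ICC of GP summaries within a PCC are assumptions. DE = 1 + (k − 1) × ICC.

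| Assumed ICC | k = 8 | k = 15 |
|---|---|---|
| 0.01 | DE 1.07, error 5.8% | DE 1.14, error 6.6% |
| 0.05 | DE 1.35, error 9.2% | DE 1.70, error 13.3% |
| 0.10 | DE 1.70, error 13.3% | DE 2.40, error 20.6% |

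**2. Which outcomes have a cluster-aware method.**
- EVITA and RETIRA: yes, the multilevel logistic model.
- REGISTER: not named with the model in Statistical analysis. The abstract lists all four dependent variables before its general statement on multilevel analysis, so it may be included.
- COST: none stated. A logistic model does not apply, and the cost paragraph does not say how the groups are compared.

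**3. Paired tests.** A new start in year 2 must have had no cholesterol-lowering drug dispensed in the preceding 12 months. A year-1 starter who keeps collecting the drug therefore cannot be a year-2 new start. Only those who stopped for 12 months can reappear, so the two sets of patients are nearly disjoint and there are almost no patient pairs. RETIRA does follow one cohort, but every member is on treatment at the start, so change can go only one way and a within-arm test says little. In either case a within-arm pre/post test does not test the randomised contrast.

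**4. Percent change.** Example: a fall from 60% to 54%.
- What the label implies: (54 − 60) / 60 × 100 = −10%.
- Formula with the difference bracketed, in percentages: (54 − 60) × 100 = −600.
- Formula with proportions: (0.54 − 0.60) × 100 = −6, a percentage-point difference.
- Formula in strict operator order: 54 − 60 × 100 = −5,946.

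No reading gives the relative change.

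**The case against.** The strongest reply is that the trial's main inference already respects the clusters. Both the abstract and Statistical analysis give the intervention effect to a multilevel analysis, and the criticised tests belong to an initial descriptive step. This stands for EVITA and RETIRA. A reader might infer from the list of simple tests that the primary p-values are invalid; the text does not support that. The descriptive setting does not rescue the simple tests themselves, because they are assigned to differences between arms under a general 5% level.

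Second, the abstract aggregates the descriptive analysis by GP, which makes the patient-level error rates an upper scenario. This also stands in part. However, χ2, Fisher and McNemar tests need categorical observations, whereas a GP-level outcome is typically a percentage, so naming them points to patient data. GP summaries within a PCC may also remain correlated.

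Third, every ICC is assumed, and the 199 patients count all new treatments. RETIRA concerns only inadequate year-1 starts, so its clusters are smaller and the inflation of a simple test on it is lower. Both points are right.

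Fourth, the pairing unit is not stated. GPs and PCCs are the same units in both years, so a paired t or Wilcoxon test on their summaries can be computed. It would therefore be too strong to say that the paired tests can never be validly computed. It would likewise be too strong to say that REGISTER and COST rest on the simple tests alone: REGISTER may fall under the abstract's multilevel wording, and the method for the COST comparison is simply not given.

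Last, the percent-change formula is probably a slip for a percentage-point difference, and nobody would report −5,946. That is likely, but the label and the formula still disagree.

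**Conclusion.** The point holds within these limits. The between-arm p-values from the listed tests are not valid for a trial that randomises PCCs. Run on patients, a nominal 5% test has a true error of about 7%, 17%, 26%, 38% and 55% for assumed ICCs of 0.001, 0.005, 0.01, 0.02 and 0.05. Run on GP summaries, it is about 6% to 21% for assumed ICCs of 0.01 to 0.10 and 8 to 15 GPs per PCC. These figures assume equal cluster sizes and two-sided tests.

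COST has no stated cluster-aware comparison, and the position of REGISTER is unclear. The effect on EVITA and RETIRA is outside this finding, on the understanding that the multilevel model includes a PCC level; the article does not name the levels.

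The objection to pairing is confined to patient-level new starts in year 1 versus year 2. The percent-change definition is wrong as written and needs no assumption to show it.

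**What to change.** - Report the χ2, Fisher, t and Mann-Whitney comparisons between arms as description only, without p-values.
- Estimate the arm contrasts for EVITA, RETIRA, REGISTER and COST with methods that include PCC as a level. For COST, use a linear or generalised linear mixed model, or an analysis of PCC-level summaries.
- For new-start outcomes, replace patient-level paired tests by a group-by-period term or by adjustment for the PCC's year-1 value. If a pre/post description is wanted, pair on GP or PCC summaries and say so.
- Define percent change as (final − initial) / initial × 100, or keep the difference and call it percentage points.

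The change is to analysis wording only and needs no new data or design change. The cost is wider confidence intervals for the affected comparisons.

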#### ***Primary outcomes***

The primary study variable is improved prescription adequacy in the use of cholesterol-lowering drugs for primary prevention of cardiovascular disease according to the recommendations of ICS clinical practice guidelines, comparing the intervention group to usual clinical practice.

Two dependent variables will be analyzed to address the primary objective:

RETIRA, defined as new cholesterol-lowering drugs initiated during the year preceding the intervention, considered inadequate, and no longer prescribed after the GP receives feedback information. This variable is directly affected by the intervention because patient records included in the calculation of this variable will be precisely those that triggered the intervention feedback.

EVITA, defined as new cholesterol-lowering drugs initiated during the 12 months follow-up period and considered inadequate.

Improved prescription adequacy is defined as an increase in the RETIRA variable and decrease in the EVITA variable.

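### The EVITA model is not committed to adjusting for each centre's own pre-intervention share of inadequate starts, which the trial already holds, so precision may be lost

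*Protocol article*

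**What the plan says.** The Statistical analysis section evaluates the intervention by a fall in EVITA and a rise in RETIRA, using multilevel logistic regression with study group as the independent variable. On covariates it says only: "The analysis will be adjusted for potential predictive independent variables and, for those considered clinically relevant, for baseline values".

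Under Primary outcomes the variable is "EVITA, defined as new cholesterol-lowering drugs initiated during the 12 months follow-up period and considered inadequate". RETIRA, in the same section, is built on starts from the year before the intervention that were judged inadequate.

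Study population identifies new prescriptions from 271 centres "during the study period (October 1, 2011-September 30, 2013), as recorded in the electronic medical records system, known as ECAP". Intervention design places the feedback in the second of those two years.

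Randomization is by centre, "stratified in quartiles by a synthetic PCC quality care indicator", the EQA. The patient and GP covariates are listed under Other variables and General practitioner variables. The GP list includes EQA, EQPF (general prescribing quality) and EQR (recording quality). The centre's earlier share of inadequate lipid-lowering starts is not on either list.

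**The concern.** The trial has a full pre-intervention year of essentially the same outcome in every centre. First-year starts are identified, and they have to be classed as adequate or inadequate in both arms, because otherwise RETIRA could not be compared between arms. A centre's prescribing habit in one year is likely to be a direct predictor of its habit in the next. Using it would cost nothing in data collection.

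The baseline clause does not clearly reach this quantity. In the sentence, baseline values attach to the independent variables thought clinically relevant, whereas EVITA is a dependent variable. Nor can a generic baseline clause supply a patient-level value, since an EVITA patient is by definition a new starter in year 2. The baseline has to be built at centre or GP level, and the text does not say so. The pre/post tests elsewhere in the section (McNemar, paired t, Wilcoxon) are separate comparisons and do not adjust the between-arm effect.

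At stake is the width of the interval for one of the two primary outcomes.

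**Working it through.** **Inputs from the protocol**
- Sample size: "approximately 60,000 new statin treatments prescribed each year"; 10% loss; "Assuming 90% strength, 5% alpha error, a 1:1 ratio of control to intervention participants". All 60,000 are taken as eligible. Statistical analysis confirms the 5% level; I assume two-sided.
- Study population: 271 centres.
- After loss: 60,000 × 0.9 = 54,000 starts in the EVITA year, so 27,000 per arm and m = 54,000/271 = 199 per centre.

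**Assumptions, because the protocol gives no value**
- The inadequate share p, the ICC, and c, the correlation between a centre's true shares in the two years.

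**1. The plan's own figure.** Sample size states that a 1% difference is detectable (read as 1 percentage point) after a cluster correction of unstated size. It cannot be reproduced or refuted without p and the ICC. Ignoring clustering, the number needed per arm for 1 point at 90% power is:

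| p | needed per arm | available per arm |
|---|---|---|
| 5% | 9,030 | 27,000 |
| 10% | 18,066 | 27,000 |
| 30% | 43,704 | 27,000 |
| 50% | 52,530 | 27,000 |

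The claim therefore holds on one year's starts only at low shares: up to ICC of about 0.010 at p = 5%, and about 0.0025 at p = 10%.

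**2. Variance saved by adjusting for the centre's first-year share**
- Design effect: DE = 1 + (m − 1) × ICC
- Reliability of an observed centre share: R = m × ICC / DE
- Correlation of observed shares between years: r = c × R
- Remaining variance: 1 − r². This does not depend on p.
- Detectable difference: 3.24 × √(4p(1 − p) × DE / 54,000), multiplied by √(1 − r²) when adjusted.

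This is a normal approximation on centre shares, compared with a model that has no covariates. Differences are shown for p = 50%.

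| ICC | DE | R | c | r | variance removed | detectable difference, points |
|---|---|---|---|---|---|---|
| 0.0025 | 1.50 | 0.333 | 0.5 | 0.167 | 3% | 1.71 → 1.68 |
| 0.0025 | 1.50 | 0.333 | 0.8 | 0.266 | 7% | 1.71 → 1.64 |
| 0.01 | 2.98 | 0.668 | 0.5 | 0.334 | 11% | 2.41 → 2.27 |
| 0.01 | 2.98 | 0.668 | 0.8 | 0.534 | 29% | 2.41 → 2.04 |
| 0.05 | 10.91 | 0.913 | 0.5 | 0.456 | 21% | 4.61 → 4.10 |
| 0.05 | 10.91 | 0.913 | 0.8 | 0.730 | 53% | 4.61 → 3.15 |
| 0.10 | 20.83 | 0.957 | 0.5 | 0.478 | 23% | 6.37 → 5.59 |
| 0.10 | 20.83 | 0.957 | 0.9 | 0.861 | 74% | 6.37 → 3.24 |

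**3. The same in power.** Take the difference that the unadjusted model detects with 90% power. Power after adjustment is Φ((1.960 + 1.282)/√(1 − r²) − 1.960).
- r = 0.3: 92.5%
- r = 0.5: 3.242/0.866 − 1.960 = 1.783, so 96.3%
- r = 0.7: 99.5%
- ICC 0.0025 (r = 0.167 to 0.266): 90.8% to 92.0%

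**4. When between-centre variation dominates.** R exceeds one half when ICC > 1/(m + 1) = 1/200 = 0.005. Below that, sampling noise within centres dominates and the baseline share helps little.

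**The case against.** **A reader might infer that the plan does not adjust for baseline.** The text does not support that. The quoted sentence permits baseline adjustment, and a centre's earlier inadequate share could count as a potential predictor. The section also speaks of a decrease in EVITA and of change from baseline. What stands is narrower: the plan makes no commitment, and nothing says in what form a baseline of EVITA would enter.

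**A reader might infer that chance baseline imbalance biases the result.** It does not. At p = 50% and ICC 0.05 the arms' first-year shares would differ by chance with a standard deviation of 1.42 points. That variation is already in the standard error of the randomised comparison, so counting it beside lost precision would count one cost twice. A simulation under the same assumptions gave type I error of about 0.05 with and without the baseline term.

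**The comparator flatters the gain.** The planned model is adjusted for patient and GP variables, including EQPF and EQA, and EQA quartiles stratify the randomisation. These may absorb part of the between-centre variation. This stands, and the remaining gain cannot be computed from the protocol. But EQA is an overall care score and EQPF covers prescribing in general; neither is the quantity EVITA measures.

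**The gain is small where the plan's 1% claim roughly holds.** At p = 10% and ICC 0.0025 the variance falls by 3% to 7%. The Sample size section also names 10% as clinically relevant. Read as percentage points, that is detectable with about 99.9% power or more without adjustment at p = 50%, even at ICC 0.10. Both points stand and limit the importance of the concern.

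**A condensed article may leave covariates to a fuller plan.** That is true of a covariate list as such. Here, however, the article states an adjustment rule and lists candidate covariates, and both pass over the most direct baseline available.

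**Conclusion.** The point holds as a missed gain in precision, not as an error that threatens validity. The protocol leaves baseline adjustment of EVITA to judgement. It does not commit the model to the one baseline that can exist for this outcome, although that baseline follows from data already needed for RETIRA.

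Against a model without covariates, the variance saved is about 11% to 74% over ICC 0.01 to 0.10 and year-to-year correlation 0.5 to 0.9. It is only 3% to 7% at ICC 0.0025 and correlation 0.5 to 0.8. The gain beyond EQPF, EQA and the other planned covariates is smaller by an unknown amount. The ICC and year-to-year correlation are assumptions throughout, as is the 50% share behind the detectable differences. The change is worth making because it is nearly free, but the trial does not depend on it.

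**What to change.** In Statistical analysis, state for EVITA that the multilevel logistic model includes as fixed covariates:
- each centre's inadequate share of new starts from 1 October 2011 to 30 September 2012, for example as centred empirical log-odds;
- the EQA stratum used in the randomisation.

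Classify the first-year starts by the same adequacy rule, using only inputs dated before 1 October 2012 so that feedback cannot influence the covariate. If the 12-month window for the risk calculation is meant to run past treatment initiation, this cut-off shortens it for late first-year starts. The covariate is then a slightly different measure from EVITA and may correlate with it less, but it remains a valid baseline. Report the result without the baseline term as a sensitivity analysis.

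The cost is one sentence and one derived variable from data already extracted, with no new patients or data. The adjusted odds ratio is conditional on the centre's baseline and may differ in size from the one without it, which is a further reason to show both.

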### Research ethics

The study will follow the national and international norms defined in the Declarations of Helsinki and Tokyo, as well as the recommendations of the Clinical Research Ethics Committee (CEIC) of our research institute, the Institut Universitari d’Investigació en Atenció Primària (IDIAP) Jordi Gol. Confidentiality of personal data is guaranteed for all participants in accordance with Spanish Law (*LOPD: Ley Orgánica de Protección de Datos de Carácter Personal 15/1999, 13 December*).

The data included in the SIDIAP database are anonymized and identified only by an internal code, created when the record is created; personal identification of patients by the research team is impossible. All PCC will be informed about the study outcomes.

To further guarantee confidentiality, SIDIAP has a protocol for linking records with external databases such as the CMBD-AH, and information provided by SISAP does not contain patient-identifying data. The procedure used consistently by SISAP is that anonymized codes are assigned, which the ECAP system decodes when information is provided to professionals responsible for that patient’s care.

